#### Follow-up and dropping out

2.3.2

All participants will be followed up regularly as per schedule (Table 1) every 3 months for the first 3 years after surgeries. If necessary, biopsy and MRI will be performed to assess local or distant recurrence.

**Table 1 T1:**
[figure not shown]
The schedule of follow-up after surgery.

Despite of written informed consent, patients are aware that they are free to discontinue their participation any time after it begins if:

1)the participant is not willing to continue on his or her own for any reason;2)adverse events which cannot be tolerated occur;3)the investigators remove a participant off for his or her good;4)the participant acquired some other treatment privately which will disturb the observation of this trial;5)pregnance happens to the participant during this trial, or6)the participant's adherence is poor.

### Outcome measures

2.4

The primary outcomes of this trial are to be scores of European Organization for Research and Treatment of Cancer QoL questionnaire-core 30 (QLQ-C30), QoL questionnaire-colorectum 29 (QLQ-CR29), Wexner Incontinence Score, International Prostate Symptom Score (for male), International Index of Erectile Function-5 (for male) and Female Sexual Function Index (for female). General QoL is assessed basically by scores of European Organization for Research and Treatment of Cancer QLQ-C30 version 3.0^[24]^ and QLQ-CR29.^[25]^ Defecation functions (daily defecation, frequency, urgency, incontinence, differentiation between defecation and gas emission, pad use, antidiarrheal drug use, and the presence or absence of erosion around the anus) are evaluated by the Wexner Incontinence Score.^[26]^ Sexual function for men and women is assessed by using the International Index of Erectile Function-5^[27]^ and Female Sexual Function Index,^[28]^ respectively. Urinary function is assessed by using the International Prostate Symptom Score^[29]^ for men and color ultrasonography of residual urine volume for all.

The secondary outcomes include incomplete CRM rate, 3-year local recurrence, 3-year disease-free survival, 3-year overall survival, and other surgical outcomes. Incomplete CRM is defined as tumor within 1 mm from closest mesorectal fascia, or within 1 mm from closest levator muscle, or invasion into or beyond the insphincteric plane. Local recurrence is defined as recurrent disease in the pelvis or at the incision. Disease-free survival is defined as the time of surgery to recurrence or end of follow-up. Overall survival is defined as the time of surgery to the date of death from any cause or the end of follow-up. Surgical outcomes include operation time, intraoperative blood loss, temporary stoma, intraoperative perforation, time to first flatus, time to liquid diet intake, postoperative hospitalization days, postoperative complications, incidence of urinary retention, and postoperative mortality in 30 days.

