## Introduction

1

Colorectal cancer is the fourth most commonly diagnosed malignancy and the second predominant cause of cancer-related death worldwide.^[1]^ According to the data from the International Agency for Research on Cancer (IARC), rectal cancer would rank 8th in terms of incidence, accounting for approximately 40% of Colorectal cancer and constituting a severe global public health burden. Surgery is still the cornerstone of curative intent treatment for rectal cancer.^[2]^ Without regard to lower rectal cancer (LRC), it is undoubtful that anterior resection (AR) is the preferred surgical procedure for mid-upper rectal cancer.^[3]^ Abdominoperineal excision (APE) firstly reported by Ernest Miles in 1908 has long been considered the “gold standard” surgical management for LRC.^[4,5]^ Proven unappealing oncologic outcomes in APE compared to AR from several large-scale case series on resected rectal specimen, Holm et al presented a new approach of extended APE, also known as extralevator APE (ELAPE), without waist to reduce the risks of circumferential resection margin (CRM) involvement and intraoperative perforation for advanced tumors.^[6–8]^ Since Schiessel et al proposed their initial experience with intersphincteric resection (ISR) for LRC,^[9]^ a promising alternative to APE without permanent colostomy, the indication for ISR has been gradually assessed and strictly applied. Meanwhile, laparoscopic-assisted minimally invasive surgery is expected to allow meticulous precise operation with good visualization in narrow pelvic cavity.^[10]^

However, with the widespread adoption of neoadjuvant chemoradiation therapy (nCRT), management of LRC has shifted significantly.^[11,12]^ Yet, whether ultimate sphincter-preserving procedures, such as ISR, offer equal or better oncologic outcomes to LRC patients after favorable response from nCRT becomes controversial compared to APE or ELAPE.^[13,14]^ Surgery for LRC has to maintain a balance between radical tumor removal to minimize the risk of locoregional recurrence and patients’ desire, or postoperative quality of life (QoL).^[15,16]^ Postoperative continence is one of important outcome measures of QoL for LRC patients, and there are conflicting reports on the functional outcomes and QoL for patients after ISR compared to APE.^[16–19]^

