#### Interventions

2.3.1

After assignment, patients in the L-ISR group will undergo standard L-ISR surgeries, while patients in the L-ELAPE group will undergo standard L-ELAPE surgeries with no intraoperative position change. Prophylactic ileostomy will be performed for selected patients with higher risk of anastomotic leakage in the L-ISR group. The radical laparoscopic-assisted surgery with meticulous total mesorectal excision and pelvic automatic nerve preservation (PANP)^[21–23]^ will be performed independently by 2 experienced and highly-specialized surgeons from the Department of Gastrointestinal Surgery, West China Hospital. Adjuvant chemotherapy, consistent with the preoperative neoadjuvant chemotherapy strategy for every participant, will continue within 4 to 6 weeks following surgery till completing 8 cycles. Closure of the ileostomy will be performed within 3 to 6 months after L-ISR according to rigorous preoperative assessment by digital rectal examination, colonoscopy, and barium enema examination.

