## Discussion

3

Currently, the hot issue of the treatment for LRC located within 5 cm from anal verge is still being debated worldwide. The rapid improvement of surgical techniques and devices and universal utilization of preoperative treatment brings not only opportunities to management of LRC but new challenges to overcome. There is much controversy, however, on a new question as to which surgical option is more appropriate for patients with LRC after favorable response to nCRT to obtain better postoperative QoL and survival outcomes.

Although recent reports suggest that ultimate sphincter-preserving procedures, including ISR, may be feasible to cure LRC without compromise of resection margins and subsequent survival outcomes,^[13,33]^ advanced surgical technique is indispensable for ISR to deliver oncologic efficacy. There is a steep learning curve to successfully completing the L-ISR or L-ELAPE operation, including precise knowledge of rectal anatomy and its anomalies, to avert injury to critical adjacent structures. Perineal wound complications will be attached great importance on and biomaterial as a novel alternative will be used for pelvic floor reconstruction in the L-ELAPE group of our study. As for ISR, anastomotic leakage and anastomotic stricture must be taken into further consideration.^[34,35]^ Thus, prophylactic ileostomy will be performed for selected patients with higher risk of anastomotic leakage and digital rectal examination monthly after surgery is necessary in the L-ISR group.

Given the evident psychological and social impact of permanent colostomy required by APE surgeries, ISR was developed to provide a sphincter-preserving alternative.^[36,37]^ However, recent studies have challenged the assumption that global QoL is worse in patients with permanent stomas (eg, ELAPE patients).^[18]^ A matched-pair analysis comparing the long-term functional outcomes and QoL for 2 post-surgical populations indicated that ISR was associated with higher frequency of diarrhea and constipation than APE.^[16]^ Postoperative continence is exactly an important clinical outcome for LRC patient. Therefore, the pros and cons of each procedure will be discussed with patients and their families before decision making in our study. Psychological guidance, incontinence and stoma care education, and instruction of sphincter exercises will be added into the follow-up for both groups.

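### The Wexner incontinence score is a primary outcome for both groups, although L-ELAPE leaves a permanent stoma, so a postoperative between-group comparison has no interpretable control value

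*Protocol article*

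**What the plan says.** Section 2.4 of the protocol article (Outcome measures) lists six primary instruments: QLQ-C30, QLQ-CR29 and then "Wexner Incontinence Score, International Prostate Symptom Score (for male), International Index of Erectile Function-5 (for male) and Female Sexual Function Index (for female". The sex-specific instruments carry their restriction in brackets; Wexner carries none. The section then lists eight aspects of defecation, ending with "differentiation between defecation and gas emission, pad use, antidiarrheal drug use, and the presence or absence of erosion around the anus", and says that they "are evaluated by the Wexner Incontinence Score". No group is named.

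On stoma status, the Introduction calls intersphincteric resection "a promising alternative to APE without permanent colostomy" and presents ELAPE as an extended form of APE. The Discussion refers to the "psychological and social impact of permanent colostomy required by APE surgeries" and to the assumption that "global QoL is worse in patients with permanent stomas (eg, ELAPE patients".

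On the use of the outcomes, the Introduction states the aim as comparing quality of life between the two operations. Section 2.5 describes a non-inferiority study with quality of life among its main measures. Section 2.7 plans tests between the two groups, in general terms and without an exception for Wexner.

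For L-ISR, section 2.3.1 gives a protective ileostomy to selected patients: "Closure of the ileostomy will be performed within 3 to 6 months after L-ISR".

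**The concern.** A primary outcome of a two-group trial must have a meaning in both groups. The Wexner score, as the article uses it, mainly describes how the anus works. One of the two operations ends with a permanent stoma. Whatever is entered on the form for those patients after surgery is a convention and not a measurement.

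At stake is the meaning of one primary result. A comparison of the two groups could favour either operation according to the convention chosen, and it could do so with apparent statistical precision. The exposure is greater because outcome assessors know the assignment (section 2.6). The Discussion itself treats continence as an important outcome for these patients, so the result would be read with attention.

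**Working it through.** The plan gives no figure for Wexner (no expected mean, standard deviation or margin), so there is no calculation to reproduce. The check is a reading of the text, followed by short arithmetic to show the size.

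**1. Which aspects can a stoma patient answer?** Of the eight listed in section 2.4, five depend on the anus: urgency, incontinence, telling stool from gas, pad use and erosion around the anus. Three could still be reported in some form with a colostomy: the daily pattern, the frequency, and use of antidiarrheal drugs. A total built on the latter three is not a measure of anal continence.

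**2. How many patients are affected?** Section 2.5 plans 72 evaluable patients per group with a group ratio of 1, so 72 / (72 + 72) = 50%. This is a planning figure, since patients choose their operation (section 2.1).

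**3. What would a two-group comparison estimate?** Let m be the mean L-ISR score and c the value assigned to L-ELAPE patients. Assume that higher is worse and that the scale runs from 0 to a maximum M; the article gives neither direction nor range. The difference is d = m − c.

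- c = 0 (no incontinence): d = m, so L-ISR looks worse.
- c = M (complete incontinence): d = m − M, so L-ISR looks better.
- L-ELAPE missing: d is undefined and there is no control group.

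The sign changes where c = m. The article states none of these codings; they mark the ends of what is possible.

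**4. How precise would that artefact look?** Suppose every L-ELAPE patient gets the same value, so that group has variance 0, and let s be the standard deviation in L-ISR. With n = 72 per group:

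- pooled variance = (s² + 0) / 2 = s²/2
- standard error = √(s²/2 × 2/72) = s/√72 = 0.118 s
- approximate 95% half-width = 1.96 × 0.118 s = 0.23 s

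Any assigned value more than about 0.23 standard deviations from the L-ISR mean would give a nominally significant difference. The comparison is then in effect a one-sample test of L-ISR against a chosen constant. (Section 2.7 as printed pairs the t test with categorical data and the chi-square test with continuous data; I take the t test to be meant for scores.)

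**5. Temporary ileostomy in L-ISR.** Visits are every 3 months for 3 years (section 2.3.2), so 36 / 3 = 12 visits. Closure at 3 to 6 months affects the first one or two of these, and only in the diverted patients, whose share is not stated.

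**The case against.** The strongest reply is that no sentence announces a Wexner comparison between the groups. Section 2.4 says only what the score evaluates, and section 2.7 is one general paragraph. The follow-up schedule (Table 1) and the flow diagram (Figure 1) are not shown and might limit the form to L-ISR. How to record an item that does not apply is commonly left to the case report form or the analysis plan.

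Part of this stands. The between-group test is an inference from the primary status of the score, the comparative aim and the two-group analysis. The absence of a coding rule is not itself a fault of the article. What does not fall away is the choice of outcome: the article lists Wexner as primary for the whole trial, and no scoring rule can create anal continence data after L-ELAPE. If a restriction exists elsewhere, the outcome section should carry it, as it does for the instruments limited by sex.

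A reader might infer more than the text supports:

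- *That L-ELAPE patients have no valid score at any time.* A preoperative score could be valid in both groups; the problem is postoperative.
- *That nothing in the domain exists after L-ELAPE.* Three of the eight listed aspects are not purely anal.
- *That a misleading result is certain.* If L-ELAPE scores are simply left missing, there is no bias in either direction, only no comparison.
- *That exactly half the trial is affected.* The split follows patient choice.

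**Conclusion.** The point holds for the postoperative Wexner score. As the article fixes it, one of six primary instruments cannot give an interpretable between-group result, because one group, planned at 72 of 144 evaluable patients, has no anal continence to score. The ileostomy point is real but secondary and confined to early visits in some L-ISR patients.

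The conclusion rests on two things: the article's own statements that APE requires a permanent colostomy and that ELAPE patients have permanent stomas, and the inference that a primary outcome of this comparative trial is to be compared. The 0.23 standard deviation figure further assumes equal groups of 72 and one common value for all L-ELAPE patients; it shows the scale of the problem and does not predict a result.

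It would be wrong to extend the point to the whole set of primary outcomes. The other five instruments are not touched by this argument, and the sample size is based on the incomplete circumferential resection margin rate, so it does not depend on Wexner.

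**What to change.** In section 2.4, take the Wexner score out of the between-group primary outcomes and state that it is reported in L-ISR only. Report it descriptively with a confidence interval, using assessments after ileostomy closure in diverted patients and all postoperative assessments in the others. Express it as change from a preoperative score only if one is collected; the visible text does not say so.

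Base the between-group primary quality-of-life comparison on a scale that both groups can answer, for example one named QLQ-C30 scale at a named time point. Add to section 2.7 that Wexner is excluded from the two-group tests.

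The cost is a change of wording in the outcome and analysis sections, and the loss of one between-group comparison that could not have been interpreted. Neither treatment nor the sample size calculation changes.

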### Study design

2.1

The study protocol follows the standard protocol items: recommendation for interventional trials (SPIRIT) guidelines.^[20]^ This is a prospective, single-central, non-randomized, non-blinded, phase I/II clinical controlled trial. All eligible patients will be assigned into 2 comparison groups (the L-ISR group and the L-ELAPE group) according to their own will after detailed preoperative conversations. The flow diagram of this trial is shown in Figure 1. Our trial started from September 2018 in West China Hospital of Sichuan University and is expected to end in 2021.

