### Sample size

2.5

This is a non-inferiority verification study with QoL and efficacy as the main index. In the pilot study, incomplete CRM rate was 6.1% (2 out of 33 patients) in the L-ELAPE group. Based on the previous studies, we assume that the rate of incomplete CRM in the L-ISR group was 8.1% which was the average value in the meta-analysis.^[30]^ The adjusted formula below is used to calculate the sample size^[31]^ (Fig. 2). The “Pe” and “Pc” are the rates of incomplete CRM of the experiment group and the control group, respectively. The “k” represents the ratio of 2 groups’ sample sizes which equals 1 in this trial and “p” represents the joint probability. Setting type I error probability **α** = 0.025, type II error probability **β** = 0.2, the sample size required for each group is 72 cases. Furthermore, we assume that there will be a 20% dropout rate. Therefore, at least 159 patients are needed in this specific trial.

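### A single landmark-based definition of incomplete CRM serves both operations, so an L-ELAPE specimen with a clear cut surface can be scored as incomplete

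*Protocol article*

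**What the plan says.** Section 2.4 (Outcome measures) gives one definition for both groups: tumor within 1 mm of the mesorectal fascia, "or within 1 mm from closest levator muscle, or invasion into or beyond the insphincteric plane" (the last landmark is taken here to mean the intersphincteric plane). The limbs are alternatives, so any one is enough. The article gives no arm-specific reading.

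The same section lists the outcome as secondary: "The secondary outcomes include incomplete CRM rate, 3-year local recurrence". Section 2.5 (Sample size) nevertheless describes a non-inferiority study and sizes it on this rate. For the control arm, "incomplete CRM rate was 6.1% (2 out of 33 patients) in the L-ELAPE group"; for L-ISR, 8.1% is taken from a meta-analysis. With α = 0.025 and β = 0.2, the result is 72 per group.

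The Introduction presents the control operation as an extended excision, "also known as extralevator APE (ELAPE), without waist to reduce the risks of circumferential resection margin (CRM) involvement". Section 2.1 assigns patients "according to their own will after detailed preoperative conversations".

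**The concern.** A resection-margin outcome should say whether tumor reaches the surface that the surgeon cut. The stated rule asks where the tumor lies relative to fixed anatomy. The two questions have the same answer only where the landmark is also the cut surface, and the two operations are cut in different places.

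If the rule counts some L-ELAPE patients whose cut surface is clear, the control rate is too high and the difference between the arms looks smaller than it is. In a non-inferiority comparison that works in favor of the experimental operation. It would also hide part of the margin benefit that the Introduction gives as the reason for the extralevator approach.

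**Working it through.** **Step 1. Set each limb against each operation.** Where the surgeon cuts is inferred from the procedures' names and from the Introduction; the article does not spell it out.

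| Limb of the definition | L-ISR | L-ELAPE |
|---|---|---|
| Within 1 mm of mesorectal fascia | At the dissection surface (mesorectal excision planned in both arms, section 2.3.1) | The same |
| Within 1 mm of levator | Levator stays behind, so it borders the cut surface | Cut is outside the levator, so the surface can be clear |
| Into or beyond intersphincteric plane | The plane is the cut surface | The plane lies inside the specimen, so the surface can be clear |

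The first limb is comparable between arms. The second and third are not, and their over-count falls on L-ELAPE.

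**Step 2. Can eligible patients meet these limbs?** Section 2.2.1 admits tumors up to 5 cm from the anal verge and stages up to cT3. Section 2.2.2 excludes invasion of adjacent structures. Its examples name neither levator nor sphincter, and closeness to them is not excluded. Such cases are limited but possible.

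**Step 3. The plan's own figure.** No non-inferiority margin is printed and the formula image is not available, so 72 cannot be confirmed. With the usual formula, pooled p = (0.061 + 0.081)/2 = 0.071 and

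n = 2p(1 − p)(1.960 + 0.842)² / d² = 0.1319 × 7.849 / d².

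At d = 0.12 this is 1.0354/0.0144 = 71.9, which rounds up to 72. A d of 0.12 follows from a 14-point margin less the 2-point expected difference, from 12 points with that difference ignored, or from 10 points with it added. A 10-point margin with the difference subtracted needs 1.0354/0.0064 = 161.8, or 162 per group. The margin is therefore an assumption, carried below at 10, 12 and 14 points.

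**Step 4. Illustration of the effect.** Let M be the assumed margin and x the assumed share of L-ELAPE patients with a clear cut surface who are scored incomplete. Take 6.1% as the true cut-surface rate in L-ELAPE and let L-ISR be worse by the whole margin, pE = 0.061 + M. The recorded control rate is 0.061 + x. The chance of concluding non-inferiority is

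Φ(x/SE − 1.960), with SE = √{[(0.061 + x)(0.939 − x) + pE(1 − pE)]/72}.

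Example, M = 0.14 and x = 0.05: SE = √[(0.111 × 0.889 + 0.201 × 0.799)/72] = 0.0600; 0.05/0.0600 − 1.960 = −1.127; Φ = 13.0%.

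| x | M = 10 points | M = 12 points | M = 14 points |
|---|---|---|---|
| 0 | 2.5% | 2.5% | 2.5% |
| 2 points | 5.6% | 5.5% | 5.4% |
| 5 points | 14.0% | 13.4% | 13.0% |

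In patients, 2 points is 0.02 × 72 = 1.4 and 5 points is 0.05 × 72 = 3.6. The result depends little on the margin and strongly on x.

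**The case against.** The strongest reply is that none of this can be measured from the article, and that part stands. Both M and x are supplied by the reviewer. The article describes no non-inferiority test on CRM; section 2.7 lists only general methods, so the test above is also assumed. Staging limits, the exclusion of adjacent invasion and the restriction to favorable responders all reduce the number of affected tumors. The outcome is secondary. Choice of operation by the patient confounds any margin comparison whatever the definition, although it could also concentrate tumors close to the levator in L-ELAPE and enlarge the problem.

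A reader might take x to 10 points and quote a false-positive chance of 34.5% at a 14-point margin. The documents do not support that figure. If the pilot used the section 2.4 definition, its 6.1% already contains the landmark-only cases, and on the point estimate x cannot exceed about 6 points. The pilot is small (2/33, exact 95% interval 0.7% to 20.2%), so this is no hard limit, but nothing supports 10 points either. In that case the planning rate would also match the endpoint as defined and would not be too low for it. The arms would still not be comparable.

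It can also be said that how specimens are read belongs in a fuller protocol or pathology manual. That would excuse silence. Here the article states a definition, and it contains no reference to the cut surface.

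**Conclusion.** The definition is wrong as written for comparing these two operations. Followed literally, it records margin involvement in L-ISR and partly local tumor extent in L-ELAPE. The likely direction is a higher L-ELAPE rate and a comparison that favors L-ISR.

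The size is unknown. The rise from 2.5% to about 5-14% is illustrative. It rests on 72 per group, one-sided 0.025, assumed margins of 10 to 14 points, an assumed over-count of 2 to 5 points, and 6.1% as the true cut-surface rate in L-ELAPE. A reader might infer that clear L-ELAPE margins will certainly be miscounted and that the comparison is already tilted by a known amount. The article does not show how specimens will be read in practice, and it only implies that the levator and sphincter leave with the L-ELAPE specimen, so neither inference is established.

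This should be fixed. It is not a fatal flaw, because the outcome is secondary; it is not trivial, because the sample size rests on it.

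**What to change.** In section 2.4, define incomplete CRM in both arms as tumor within 1 mm of the actual resection surface of the specimen at pathology, whichever structure forms that surface. Keep the relations to mesorectal fascia, levator and intersphincteric plane as descriptors of tumor extent, reported by arm.

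In section 2.5, state whether the 6.1% and 8.1% rates were obtained with that definition. If not, restate the basis of the sample size.

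The cost is one definition and one pathology item on the case report form, with no extra procedure and no change to treatment. Enrollment began in September 2018, so the new item should be completed for patients already operated on before the arms are compared. That may mean re-reading some pathology reports, and the 33 pilot reports if their definition is unclear.

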### Data collection, management, and statistical analyses

2.7

For purpose of acquiring high-quality monitoring, we plan to employ several professional clinical investigators to collect and manage the data of all participants during entire trial performing. A Case Report Form (CRF) is designed for each participant to document their data. And we will upload the data of all participants to Research Manager (ResMan), an Electronic Data Capture (EDC) system, and the individual patient data (IPD) will be publicly accessed via Chinese Clinical Trial Registry (ChiCTR.org) within 3 years after completion of this trial.

SPSS for Windows, version 22.0 (IBM Corp, Armonk, NY) will be used for statistical analysis. The data are presented as the mean value **±** standard deviation for continuous variables and as a number for categorical variables. The difference of categorical data and continuous data will be compared with Student *t* test and chi-square test between the 2 groups, respectively. The Kaplan–Meier estimate will be used to analyze survival and fit survival curves. The multiple factor analysis will be performed by using Cox regression model.

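### Disease-free survival is defined with recurrence as its only event, so deaths without recurrence are censored and the endpoint is really time to recurrence

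*Protocol article*

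**What the plan says.** Section 2.4 (Outcome measures) places DFS among the secondary outcomes: "The secondary outcomes include incomplete CRM rate, 3-year local recurrence, 3-year disease-free survival, 3-year overall survival, and other surgical outcomes". It then defines it: "Disease-free survival is defined as the time of surgery to recurrence or end of follow-up". The sentence that follows gives the companion endpoint: "Overall survival is defined as the time of surgery to the date of death from any cause or the end of follow-up". The same section lists "postoperative mortality in 30 days" among the surgical outcomes.

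Follow-up visits take place "every 3 months for the first 3 years after surgeries" (section 2.3.2). For the analysis, section 2.7 says "The Kaplan–Meier estimate will be used to analyze survival and fit survival curves" and adds a Cox model for the multiple-factor analysis. Nothing elsewhere in the article adds death to the DFS events.

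**The concern.** DFS is normally read as the probability of being both alive and free of disease. The written definition covers only the second part. A patient who dies without recorded recurrence has no DFS event, so the follow-up time simply ends there. A 3-year figure obtained this way answers how often the tumour returns, with deaths removed by censoring, yet it would be published under a name that promises more.

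Two consequences follow. First, the figure is too favourable in each group whenever anyone dies without recurrence. Second, the excess need not be equal in the two groups. Patients choose their own operation, so age, fitness and operative or other non-cancer mortality may differ between L-ISR and L-ELAPE. A difference in such deaths would leave no mark on the DFS comparison. This matters because survival is part of the stated aim of the trial, and section 2.5 frames the trial as a non-inferiority study in which efficacy is one of the main indices.

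**Working it through.** **Step 1: does the wording exclude death?** In the overall survival sentence, death from any cause and the end of follow-up are two separate items. End of follow-up is therefore not the article's term for death. The DFS sentence has recurrence and end of follow-up only, so death is left out. If end of follow-up had been meant to cover death in DFS, the sentence would merge an event with a censoring time and would still need correction.

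**Step 2: what does the planned analysis do with such a patient?** With Kaplan–Meier and recurrence as the only event, a patient who dies without recurrence leaves the risk set at death as a censored observation. The 30-day mortality outcome shows that the protocol itself allows for early deaths of this kind.

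**Step 3: how large is the effect?** The article states no DFS rate, recurrence rate, death rate or hazard ratio, so there is no figure to reproduce. The size can only be illustrated. Assume two independent constant hazards, with net 3-year recurrence risk r and net 3-year risk of death without recurrence d.

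- As written (deaths censored): 1 − r
- With death as an event: (1 − r) × (1 − d)
- Overstatement: (1 − r) × d

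Assumed ranges: r = 15% to 35%, d = 1% to 10%.

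| r | As written | d = 1% | d = 5% | d = 10% |
|---|---|---|---|---|
| 15% | 85.0% | 84.15% (0.85 points) | 80.75% (4.25) | 76.5% (8.5) |
| 25% | 75.0% | 74.25% (0.75) | 71.25% (3.75) | 67.5% (7.5) |
| 35% | 65.0% | 64.35% (0.65) | 61.75% (3.25) | 58.5% (6.5) |

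Each cell gives 3-year DFS with death as an event and, in brackets, the overstatement. The range runs from 0.65 × 0.01 = 0.65 points to 0.85 × 0.10 = 8.5 points. It is zero only if nobody dies without recurrence.

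**Step 4: the comparison between groups.** Suppose r = 25% in both groups, with d = 2% in one and 5% in the other. As written, both groups show 75.0% and the difference is 0. With death as an event they show 0.75 × 0.98 = 73.5% and 0.75 × 0.95 = 71.25%, a difference of 2.25 points that the written endpoint does not contain.

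**Step 5: does this touch the sample size?** No. Section 2.5 builds it on the incomplete circumferential resection margin rate ("incomplete CRM rate was 6.1% (2 out of 33 patients) in the L-ELAPE group"), from which "the sample size required for each group is 72 cases". DFS does not enter.

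**The case against.** The strongest case on the other side concerns weight. DFS is one of several secondary outcomes. The primary outcomes are quality-of-life and function scores, and no stated success criterion rests on DFS. Eligibility holds down deaths from other causes: age up to 75, ASA I–III, ECOG 0–2, with prior malignancy, severe lung disease and ischaemic heart disease excluded. With 72 patients per group and an illustrative 75% DFS, the standard error, ignoring censoring, is √(0.75 × 0.25 / 72) ≈ 5.1 points per group, or about 5.1 × √2 ≈ 7.2 points for the difference. A bias of 1 to 3 points lies well inside that, and whatever part is common to both groups cancels in the comparison. All of this stands. It lowers the severity but does not make the definition right.

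A reader might also infer more than the article supports:

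- **That patients who die are carried as disease-free to 3 years.** Under Kaplan–Meier they are censored at death. Counting them as disease-free would require a simple proportion, which is not the stated method. Under the assumptions above, that would overstate DFS by 0.8 to 9.2 points, in the same direction.
- **That a mortality difference between the operations would be concealed altogether.** It would be missing from DFS only. Overall survival counts death from any cause, and 30-day mortality is reported separately.
- **That reported DFS will exceed overall survival.** The written definition permits this, which cannot happen when death is a DFS event. But with 25% recurrence, 3-year overall survival would have to fall below 75%, and nothing in the article suggests so.
- **That the 3-year local recurrence analysis is also wrong.** The article does not say how that rate will be estimated, and such detail may properly sit in an analysis plan that is not shown.

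It could also be said that a condensed article shortened a fuller event definition. That is weak here, because the adjacent sentence does name death.

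**Conclusion.** The definition is wrong as written for the name it carries. The endpoint is time to recurrence with deaths censored, and it overstates 3-year DFS whenever a patient dies without recurrence. The direction is certain; the size is not. The range of about 0.7 to 8.5 points rests wholly on assumed rates and on independence of the two hazards. If frailty raises both risks, censoring at death is informative, and the curve no longer estimates even the net recurrence risk cleanly. Unequal bias between the groups is plausible because patients choose their operation, but the article gives no evidence of its size.

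This is a should-fix correction to a secondary endpoint. It does not affect the primary outcomes or the number of patients.

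**What to change.** Replace the DFS sentence in section 2.4 with a definition such as: time from surgery to the first of local recurrence, distant recurrence or death from any cause; patients alive and recurrence-free are censored at their last disease assessment.

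If the sponsor does want the present quantity, it should be called time to recurrence and not reported as DFS.

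The cost is one sentence. Deaths are already collected for overall survival and the 3-monthly visits already supply the assessment dates, so no new data are needed. Reported DFS will look slightly less favourable. The change should be made and dated before outcome data are analysed, since a later change of event definition would look data-driven.
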